### Statistical analysis

An intention-to-treat analysis will be completed for participants in all arms. Demographic characteristics will be compared between groups using Student’s *t* test or Mann–Whitney tests for continuous data and Pearson’s chi-squared test for categorical data as appropriate. For continuous variables, results will be presented as means and standard deviations. The number and percentage will be presented for categorical and binary variables. Following distributional checks, log transformations will be carried out as needed. For the primary and main secondary glycaemic outcomes, an adjustment will be made using multiple linear regression (method analysis of covariance; ANCOVA [42]). For yes/no outcomes, binomial regression will be used with a log link to give risk ratios. For other outcomes, where there is no baseline value, adjustment will be made for the primary outcome only. Analytes measured from a targeted NMR metabolome will be checked for normality; those with non-parametric distribution will be log-transformed. Analyte data at baseline and at the time of the diagnostic OGTT (24–28 weeks) will be compared between women who received the intervention and those who did not. To test for the effect of the intervention on dietary and physical activity outcomes, ANCOVA will be used adjusted for trial entry measurements.

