#### 13–15^+6^ weeks’ gestation appointment: baseline and randomisation

At the first appointment, informed consent will be obtained by the chief investigator from women to be randomised into the trial. All participants will be fitted with a glucose sensor (Dexcom G6) to be worn for 7–10 days. The sensors are small, easy to wear, waterproof devices which require no finger prick calibration. The sensors will be applied to the back of the upper arm or abdomen of the participant and activated in blinded mode. To assess dietary intake, a semi-quantitative food frequency questionnaire (FFQ) will be administered to evaluate dietary glycaemic load (GL), glycaemic index (GI), saturated fat and other dietary variables [34]. Physical activity will be assessed by Axivity accelerometer AX3 (https://axivity.com/product/ax3).

Following the baseline assessment, randomisation will be performed electronically by the research team via a secure online-based data management platform (MedSciNet™) in order to conceal the sequence until interventions are assigned. Women will be randomised (1:1:1) into three groups:

a. Lifestyle advice

b. Lifestyle advice plus metformin

c. Standard antenatal care

The randomisation schedule will be minimised according to ethnicity (Black, White, Asian, Other), BMI (30−34.9kg/m^2^, 35−39.9kg/m^2^, ≥40kg/m^2^), parity (nulliparous/multiparous) and age. Participants will be allocated sequential study numbers regardless of allocation to the intervention or standard care group. Due to the nature of the study design, it will not be possible to blind participants or research staff to the randomisation arm.

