#### Intervention

##### Lifestyle advice

Participants allocated to the lifestyle advice or lifestyle advice plus metformin arms will receive the intervention. The dietary intervention, delivered by a nutritionist, focuses on reducing GL and saturated fat intake using a regime previously shown to be effective in changing diet in ‘all risk’ obese pregnant women [34]. The dietary component of the intervention will aim to promote a healthier pattern of eating without restricting energy intake. The dietary advice will be tailored according to the woman’s habitual diet and cultural preference.

To decrease GL, participants will be encouraged to exchange starchy foods with a medium to high GI for those with a lower GI and reduce the consumption of sugar-sweetened beverages including fruit juice. Specific dietary goals will be provided for each participant that focus on differentiating between carbohydrate-rich foods. This advice will include replacing high GI breads with lower GI breads such as granary/wholegrain/multigrain bread, sourdough and rye; replacing high GI breakfast cereals with lower GI varieties such as porridge, oat-based cereals and no-added-sugar muesli; and encouraging consumption of lower GI grains like basmati rice, pearl barley, cracked wheat (bulgur), quinoa and pasta. To reduce saturated fat intake, participants will be encouraged to swap oils and spreads high in saturated fats (butter, lard, ghee) for those high in mono- and polyunsaturated fats (olive, sunflower); swap meat high in saturated fat (fatty meats, processed meat and meat products) for lean red meat, chicken and fish; and swap higher fat dairy foods (milk, cheese, yogurt) for lower fat varieties.

The physical activity component of the intervention will focus on a safe physical activity regime using the UPBEAT strategy which was shown to be successful in improving physical activity in ‘all risk’ pregnant women with obesity [34]. The advice aims to increase incremental walking and daily step count at a moderate intensity, being more active in daily life and reducing sedentary behaviour (sitting and screen time).

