### Process evaluation

A process evaluation will be performed to investigate whether the intervention was implemented as planned and whether participants were satisfied with the intervention. The process evaluation will follow Steckler and Linnan’s framework [38]. This will explore:

1) Context (environmental, socio-economic, political factors)

2) Reach (proportion of target population that participates in the intervention)

3) Dose delivered and dose received (proportion of intervention received)

4) Fidelity (extent to which the intervention was delivered as prescribed by the protocol)

5) Acceptability (if intervention materials and advice were well received by the participants)

Qualitative, semi-structured interviews will be conducted to capture the women’s perceptions and experiences of the study. Women will be recruited (*n*=15, 5 per group) after the intervention has been provided. The interviews will be recorded and transcribed.

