#### Secondary patient-centred outcomes

A reduction in mean glucose/24h of 0.5 mmol/L after 8 weeks of treatment compared to the standard arm as assessed using CGM.Other glycaemic parameters after 8 weeks of treatment; mean daytime glucose 0.700–23.00h, mean nocturnal glucose 23.00–0.700h, percentage time in tight glucose control target 3.5–6.7mmol/L, percentage time in recommended glucose control target 3.5–7.8mmol/L, area under the curve (AUC) <6.7mmol/L, AUC <7.8mmol/L, glucose variability measures (standard deviation (SD), coefficient of variation (CV)), high blood glucose index (HBGI) and low blood glucose index (LBGI).GDM diagnosis at 24–28 weeks (in accordance with IADPSG and NICE criteria).Metabolome; a targeted high-throughput nuclear magnetic resonance (NMR) metabolomic platform (http://computationalmedicine.fi/) will be used to measure metabolites from blood samples at baseline and at the time of the diagnostic OGTT. The platform quantifies lipid measures including lipoprotein particles (VLDL subdivided into 6 subclasses, IDL, LDL subdivided into 3 subclasses and HDL subdivided into 4 subclasses), constituents within each lipoprotein particle type (triglycerides, total cholesterol, free cholesterol and cholesterol ester levels and phospholipid concentrations), fatty acids, amino acids, glycolysis related metabolites, ketone bodies and inflammatory markers.Dietary intake and physical activity, including changes in GI, GL, saturated fat, time spent in light and moderate exercise and sedentary behaviour from baseline and after the 8-week intervention.

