### Sample size calculation and loss to follow-up

The study is intended as a pilot, one of whose aims is to gather the information needed for planning the definitive trial. This includes estimating the SD of the main outcome (the difference in mean 24-h glucose between arms) and checking the distribution. With twenty participants per arm, the SD can be estimated to within 80% of the true value. A 0.5mmol/L difference in mean 24-h glucose was considered to be of biological relevance based on data from comparable studies of CGM in pregnant women with obesity [39–41]. To account for up to 25% loss to follow-up and achieve a total sample size of 60, a sample of 84 women will be recruited.

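### The planned metabolome analysis compares two groups, so as worded it pools lifestyle advice with lifestyle advice plus metformin and cannot give the effect of each intervention

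*Protocol article*

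**What the plan says.** All references are to the Protocol article.

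- The section on the 13–15+6 week appointment states: "Women will be randomised (1:1:1) into three groups". The groups are lifestyle advice, lifestyle advice plus metformin, and standard antenatal care.
- *Study objectives* lists, among the secondary objectives, finding the effect of each intervention on a targeted maternal metabolome.
- *Secondary patient-centred outcomes* says that an NMR platform "will be used to measure metabolites from blood samples at baseline and at the time of the diagnostic OGTT", so a baseline value is planned for every analyte.
- *Statistical analysis* opens with "An intention-to-treat analysis will be completed for participants in all arms". Later in the same paragraph it says that analyte data at baseline and at 24–28 weeks "will be compared between women who received the intervention and those who did not". The next sentence gives diet and physical activity an ANCOVA adjusted for the trial-entry measurement.

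Apart from the normality check and log transformation, nothing else is said about how the metabolome will be analysed.

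**The concern.** The objective asks for two effects and the stated analysis yields one. A comparison of women with and without the intervention cannot show whether lifestyle advice alone, or only the arm that includes metformin, changes the metabolome. If the two arms act differently, the pooled result describes neither.

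Two further features of the sentence need attention. First, it defines the groups by receipt, which an analyst could take literally despite the intention-to-treat statement at the head of the paragraph. Second, it treats the baseline analytes as something to compare between groups. Values taken before treatment carry no information about a treatment effect on their own. Their use is as a covariate, as the same paragraph does for diet and activity.

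**Working it through.** The article gives no effect size, SD or power for any analyte, so there is no stated figure to reproduce. The check is one of text, followed by an illustration under assumed effects.

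**1. Who is in each group.** *Lifestyle advice* says: "Participants allocated to the lifestyle advice or lifestyle advice plus metformin arms will receive the intervention". The phrase used in the metabolome sentence therefore covers both active arms. *Sample size calculation and loss to follow-up* plans on 20 evaluable women per arm ("With twenty participants per arm, the SD can be estimated to within 80% of the true value"), 60 in all. The comparison is then 20 + 20 = 40 against 20.

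**2. What it estimates.** Let d_L and d_LM be the effects against standard care of lifestyle advice and of lifestyle advice plus metformin. With equal arms the pooled contrast is (20·d_L + 20·d_LM)/40 = (d_L + d_LM)/2. If d_L = 0 and d_LM = d, this is d/2. Two different effects cannot be recovered from their average.

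**3. Illustration.** The effects are assumed, in SD units. The test is two-sided at 0.05, by normal approximation, with power counted in the direction of the effect: power = Φ(effect/SE − 1.96). The SE is √(1/40 + 1/20) = 0.274 for the pooled contrast and √(1/20 + 1/20) = 0.316 for each pairwise contrast.

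| d_L | d_LM | Pooled effect | Power, pooled | Power, lifestyle vs standard | Power, lifestyle + metformin vs standard |
|---|---|---|---|---|---|
| 0 | 0.8 | 0.4 | 0.31 | null | 0.72 |
| 0.4 | 0.8 | 0.6 | 0.59 | 0.24 | 0.72 |
| −0.4 | 0.4 | 0 | null | 0.24 | 0.24 |
| 0.8 | 0.8 | 0.8 | 0.83 | 0.72 | 0.72 |

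Pooling helps when the two effects are equal, loses power when only one arm acts, and shows nothing when they are opposite.

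**4. Precision cost of separate contrasts.** 0.316/0.274 = 1.15, so the SE is about 15% larger; the variance ratio is 0.100/0.075 = 1.33. With baseline adjustment at correlation r, the pairwise SE is about 0.316·√(1 − r²):

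- r = 0: 0.316
- r = 0.5: 0.316 × 0.866 = 0.274, equal to the unadjusted pooled SE
- r = 0.6: 0.316 × 0.8 = 0.253

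The article gives no value of r. A pooled contrast adjusted in the same way would gain too, so the offset is relative to an unadjusted pooled comparison.

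**5. Receipt or allocation.** Three places bear on the word. The intention-to-treat sentence points to allocation. So does *Lifestyle advice*, which says that allocated women will receive the intervention. *Process evaluation* uses the word for actual uptake: "Dose delivered and dose received (proportion of intervention received". The metabolome sentence also groups the baseline samples, when nobody has yet received anything, and that again favours allocation. The wording is ambiguous, with the balance towards allocation.

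**The case against.** **The singular may be shorthand.** The sentence on diet and physical activity also refers to the intervention in the singular, although the objective for those outcomes likewise concerns each intervention. *Study objectives* may show the real intent. This stands as a reason for caution, but the metabolome sentence goes further than a singular noun: it names two groups, and no other sentence supplies a contrast by arm. Taken as an instruction to an analyst, it is a pooled comparison.

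**Pooling can be efficient.** This is true when the two effects are alike (0.83 against 0.72 in the last row above). It does not answer the objective, and a pooled contrast can be kept as a supplement.

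**The model belongs in the analysis plan.** The sentence names no model and does not rule out ANCOVA, so the lack of baseline adjustment is not in itself an error. It belongs in the repair because the sentence has to be rewritten anyway.

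Two stronger readings are tempting and are not supported:

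- *That an as-treated analysis is planned.* A reader might infer that women who did not take up the intervention will be moved into the comparison group. The article defines no receipt threshold and no such population for the metabolome, and its other wording leans towards allocation.
- *That many analytes will be tested without error control.* The platform covers "VLDL subdivided into 6 subclasses, IDL, LDL subdivided into 3 subclasses and HDL subdivided into 4 subclasses", that is 6 + 1 + 3 + 4 = 14 subclasses, and five constituents are listed. A reader might count 14 × 5 = 70 measures. The constituents are given by particle type, which could equally mean 4 × 5 = 20, so the count is insecure. Multiplicity control is also commonly left to an analysis plan, and its absence from an article is not a finding.

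**Conclusion.** The point holds on the wording of *Statistical analysis*: the metabolome comparison is between two groups, pools the two active arms, and does not deliver the stated objective for each intervention. With equal arms it estimates the mean of the two effects, hence half the effect when only one arm acts. That result depends only on the 1:1:1 allocation; the power figures rest on assumed effects and on 20 evaluable women per arm.

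The conflict with intention-to-treat is a wording ambiguity to remove, not a demonstrated departure.

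Severity is moderate. The metabolome is one of several secondary outcomes in a pilot whose primary outcomes concern feasibility. It does not feed the sample size of the definitive trial, which rests on mean 24-hour glucose. Randomised arm is recorded, so the analysis by arm remains possible.

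**What to change.** Replace the sentence in *Statistical analysis* with:

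> For each analyte, the 24–28 week value (log-transformed if skewed) will be compared by randomised arm using ANCOVA adjusted for its baseline value. Lifestyle advice versus standard care, and lifestyle advice plus metformin versus standard care, will be estimated separately. Any pooled contrast of the active arms with standard care is supplementary.

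Drop the between-group comparison of baseline analytes as an effect analysis; baseline values may still be tabulated by arm. If the added effect of metformin is of interest, the contrast between the two active arms can be named in the same sentence.

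The change needs no new data and no change of design. Its cost is about 20 against 20 women per contrast instead of 40 against 20, with the loss of unadjusted precision shown in step 4 of the working.

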### Trial outcomes

#### Primary feasibility outcomes

Trial feasibility will include examination of recruitment, retention, intervention adherence, determination of sample size and acceptability. Recruitment will be determined by calculating the proportion of randomised participants from those screened for eligibility. Retention will be measured by the percentage of participants completing the study through the post-assessment. Intervention attendance will be assessed as the number of diet and physical activity sessions completed, with a range of 0 to 8. Adherence to metformin will be defined as participants taking 80% of the study prescribed medication during the trial as assessed by tablet count. The accelerometer wear time will be reported (hours/day). CGM adherence will be defined by sensor wear ≥ 70%. For future full-scale RCTs using CGM, the sample size will be calculated based on the best estimate of the standard deviation and distribution of mean 24-h glucose as determined in the pilot to detect a 0.5-mmol/L difference between arms. Intervention acceptability will be evaluated by an embedded process evaluation using qualitative research methods. Interview questions will address intervention satisfaction and usefulness in addition to ease of using study devices. Additional questions will address the women’s perceptions of risk and benefits of taking metformin, barriers to adherence and the dose of metformin that is acceptable to women. Feedback on the content of the diet and physical activity components will also be obtained in addition to the delivery format (online delivery and time involved).

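### The planned metabolome comparison merges the lifestyle and lifestyle-plus-metformin arms, so it cannot answer the objective about each intervention separately

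*Protocol article*

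**What the plan says.** All references are to the Protocol article.

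- **Study objectives.** The second of the secondary objectives concerns the effect of each intervention on a targeted metabolome. The first names lifestyle advice and metformin plus lifestyle advice as separate interventions, each set against standard care.
- **Baseline and randomisation appointment.** "Women will be randomised (1:1:1) into three groups": lifestyle advice, lifestyle advice plus metformin, and standard antenatal care.
- **Statistical analysis, opening sentence.** "An intention-to-treat analysis will be completed for participants in all arms".
- **Statistical analysis, metabolome sentence.** Analyte data at baseline and at the diagnostic glucose tolerance test "will be compared between women who received the intervention and those who did not".
- **Intervention, Lifestyle advice.** "Participants allocated to the lifestyle advice or lifestyle advice plus metformin arms will receive the intervention".

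The article gives no arm-by-arm comparison for the metabolome anywhere else.

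**The concern.** The metabolome sentence has two groups and one intervention, while the objective has two interventions and the design has three arms. A comparison of both active arms together with standard care returns one number per analyte. That number cannot show whether a change came from the lifestyle programme, which both active arms receive, or appeared only where metformin was added. An effect confined to one arm is halved, and effects in opposite directions cancel.

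This matters for the use the article makes of the pilot. Its Discussion describes the next trial as lifestyle advice with or without metformin, and a pooled metabolome result says nothing about that choice.

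A second, smaller point is the verb. Grouping by what women received, rather than by what they were allocated to, sits awkwardly beside the intention-to-treat sentence that opens the same section.

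**Working it through.** **Which groups does the sentence define?** The Lifestyle advice subsection uses the same verb and the same singular noun as the metabolome sentence, and applies them to women allocated to either active arm. Read with the article's own usage, the two groups are the two active arms combined and standard care.

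**What does that contrast estimate?** Let L be the effect of lifestyle advice against standard care on an analyte, and M the effect of lifestyle advice plus metformin against standard care, both in within-arm SD units. With equal arms the merged contrast estimates (L + M)/2. For example:

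| L | M | Merged value |
|---|---|---|
| 0 | 0.8 | 0.4 |
| 0.4 | 0.4 | 0.4 |
| -0.4 | 0.4 | 0 |

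The first two rows differ in substance and give the same result. L and M cannot be recovered from the merged value.

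**Inputs for the illustration.** The article states no alpha, power, effect size or SD for the metabolome, so there is no figure of its own to reproduce here. The Sample size section bases its reasoning on 20 women per arm ("With twenty participants per arm, the SD can be estimated to within 80% of the true value") and on a total of 60 completers ("To account for up to 25% loss to follow-up and achieve a total sample size of 60, a sample of 84 women will be recruited"). I use 20 completers per arm. The effect sizes of 0.6 and 0.9 SD and the nominal two-sided 5% level are my assumptions. There is no baseline adjustment and no multiplicity correction.

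**Standard errors.**

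- Merged, 40 against 20: sqrt(1/40 + 1/20) = 0.274 SD.
- Arm-specific, 20 against 20: sqrt(1/20 + 1/20) = 0.316 SD.

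**Case 1: only the metformin arm shifts the analyte (L = 0, M = d).** The merged contrast estimates d/2. Its signal-to-noise ratio relative to the arm-specific contrast is (0.5/0.274)/(1/0.316) = 0.58.

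**Case 2: both arms act alike (L = M = d).** The merged contrast estimates d. Its relative signal-to-noise ratio is 0.316/0.274 = 1.15.

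Power is from the noncentral t distribution, with 58 degrees of freedom for the merged contrast and 38 (two arms only) or 57 (three-arm model) for the arm-specific contrast:

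| d (SD) | Arm-specific | Merged, case 1 | Merged, case 2 |
|---|---|---|---|
| 0.6 | 46% | 19% | 58% |
| 0.9 | 79-80% | 37% | 90% |

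In case 1 the merged group would also be more spread out, because it mixes two means. The calculation ignores this, so it slightly flatters the merged contrast.

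**Receipt or allocation?** The article expects uptake to vary among allocated women. Attendance is counted as "the number of diet and physical activity sessions completed, with a range of 0 to 8", and "Adherence to metformin will be defined as participants taking 80% of the study prescribed medication". Taken literally, grouping by receipt would move an allocated woman who took up nothing into the comparison group. Against that, the Lifestyle advice subsection describes allocated women as those who receive the intervention, and no section defines a receiver for analysis. The wording is therefore ambiguous.

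**The case against.** **The singular noun may be shorthand.** The objectives themselves use the singular for the whole programme just before distinguishing the two interventions, and a condensed article can leave exact contrasts to a fuller document. This would carry weight if the article were silent. It is not: it names two comparison groups for the metabolome, and they do not match its own objective.

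**Pooling can be the better test.** Both active arms receive the same lifestyle programme. If metformin adds nothing to an analyte, pooling gains power, as case 2 shows. That stands as a reason to keep a pooled comparison as a supplement. It does not make the pooled comparison an answer about each intervention.

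**The stakes are limited.** The metabolome is a secondary outcome in a pilot whose primary aims are feasibility, and the sample was not set to power it. This stands and caps the severity.

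**Two stronger readings are tempting, and the documents do not support them.**

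- A reader might infer that the plan abandons intention to treat for the metabolome and inflates the type I error. The intention-to-treat sentence is unqualified, the article equates allocation with receipt, and the attendance and tablet-count measures are feasibility outcomes, not analysis groups. Any error rate would also depend on an assumed number of non-receivers for which the documents give no basis.
- A reader might infer that the diet and physical activity analysis has the same fault, because it too refers to the intervention in the singular. That sentence names no groups and is compatible with a three-arm analysis of covariance.

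**Conclusion.** The point holds for the metabolome sentence. As written, the analysis is a two-group contrast that averages the two active arms and cannot answer the stated objective. This mismatch follows from the text alone and needs no assumption about effect sizes.

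The practical size depends on how the arms behave. The contrast loses more than half its power if only the metformin arm acts, and gains some if both act alike; both results rest on 20 completers per arm and the assumed effects. The verb is an ambiguity to remove and is not evidence of an as-treated analysis. The sentence should be corrected, but the primary feasibility aims are unaffected.

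**What to change.** Replace the metabolome comparison sentence with wording such as:

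> Analytes at 24-28 weeks will be compared by randomised arm (intention to treat), lifestyle versus standard care and lifestyle plus metformin versus standard care, from one three-arm model; any pooled comparison is exploratory.

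This settles the contrast and ties the groups to allocation. It also prevents a choice between pooled and arm-specific results after the data are seen.

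The cost is one sentence, with no new data and no change in sample size. There will be two contrasts per analyte instead of one, each with a standard error of 0.316 SD against 0.274 SD for the pooled contrast. That loss of precision matters only if the two arms act alike.

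### Allocation is minimised on ethnicity, BMI, parity and age, but no stated model names these factors; if they are prognostic, intervals that omit them are conservative

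*Protocol article*

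**What the plan says.** In the section on the 13–15+6 weeks' appointment, the Protocol article states: "Women will be randomised (1:1:1) into three groups". It continues: "The randomisation schedule will be minimised according to ethnicity (Black, White, Asian, Other), BMI" (three bands), "parity (nulliparous/multiparous) and age". No age cut-points are given.

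The Statistical analysis section treats the outcomes in turn:

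- **Glycaemic outcomes:** adjustment by multiple linear regression (ANCOVA). No covariate is named.
- **Diet and physical activity:** "ANCOVA will be used adjusted for trial entry measurements". Nothing else is named.
- **Outcomes without a baseline value:** "adjustment will be made for the primary outcome only".
- **Yes/no outcomes:** binomial regression with a log link. No covariate is named.

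Demographic characteristics appear in that section only as variables to be compared between groups. For the later full-scale trial, Primary feasibility outcomes says the sample size will rest on the "best estimate of the standard deviation and distribution of mean 24-h glucose as determined in the pilot".

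**The concern.** Minimisation removes most of the chance imbalance in a factor from the comparison of arms. If the factor predicts outcome, the true sampling variance of the arm difference falls. A model that omits the factor does not register this gain: the factor's contribution stays in the residual variance and so in the reported standard error. Intervals then cover more often than their nominal level, and tests reject too rarely.

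With about 20 women per arm, precision is scarce. The factors are already collected and already used for allocation, so the lost precision could be recovered at almost no cost. A related matter is which SD goes into the definitive sample size, because determining that sample size is one of the primary feasibility outcomes.

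**Working it through.** **Inputs.** From the article: 60 women in three arms at 1:1:1; ethnicity in 4 groups, BMI in 3 bands, parity in 2, plus age; a 0.5 mmol/L difference for the definitive trial. The article gives no alpha, power, SD or prognostic strength, so it has no figure on this point to reproduce. Assumed: two-sided 5%, 80% power, SD 0.75 or 1.0 mmol/L, and partial R² (the share of the variance remaining after baseline that the four factors explain) from 0 to 0.30.

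**Degrees of freedom.** Intercept, two arm terms and baseline leave 60 − 4 = 56. The factors as categories, with age as one term, use 3 + 2 + 1 + 1 = 7, leaving 49. With BMI and age continuous they use at most 3 + 1 + 1 + 1 = 6.

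**Formula under exact balance.** Half-width with the factors divided by half-width without:

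(t₀.₉₇₅,₄₉ / t₀.₉₇₅,₅₆) × √(1 − R²) / √(1 − R² + R² × 59/56)

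The ratio of t quantiles is 1.003. At R² = 0.20 this gives 1.003 × 0.8944 / 1.0053 = 0.892.

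**Simulation under realistic balance.** 60 women; minimisation on all four factors, followed with probability 0.8 and otherwise simple random; two age bands; baseline correlation 0.5; 2,500 trials per row. Both models include baseline.

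| Partial R² | Ratio, exact balance | Ratio, simulated | Excess width if factors omitted (1/ratio − 1) | Coverage, omitted | Coverage, included |
|---|---|---|---|---|---|
| 0 | 1.003 | 1.022 | −2.2% | 0.949 | 0.956 |
| 0.05 | 0.976 | 0.992 | 0.8% | 0.958 | 0.948 |
| 0.10 | 0.949 | 0.966 | 3.5% | 0.955 | 0.940 |
| 0.20 | 0.892 | 0.909 | 10.0% | 0.966 | 0.950 |
| 0.30 | 0.833 | 0.850 | 17.6% | 0.974 | 0.951 |

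The Monte Carlo error of a coverage figure is √(0.95 × 0.05 / 2500) = 0.004. The over-coverage is therefore clear at 0.20 and 0.30 and within noise at 0.10 and below. The mechanism shows directly. Without the factors, the actual standard error falls from 0.275 at R² = 0 to 0.247 at R² = 0.30, while the reported half-width stays at 0.551 to 0.555.

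A second simulation with other settings (no baseline covariate, three age bands) gave mean interval widths, without and with the factors, of 1.263 and 1.218, 1.266 and 1.150, and 1.268 and 1.074 at R² of 0.10, 0.20 and 0.30. That is 4%, 10% and 18% too wide, in agreement.

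**SD for the definitive trial.** With a true within-arm variance of 1, the simulated pooled within-arm variance was 1.000 to 1.008 in every row, so minimisation does not inflate it. The residual SD of the model without the factors was 0.863 to 0.867. It is below 1 because of the assumed baseline correlation: √(1 − 0.5²) = 0.866. Adding the factors shrinks the SD by a further √(1 − R²), so leaving them out overstates the SD of a factor-adjusted analysis by 1/√0.90 = 1.05 or 1/√0.80 = 1.12.

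In women per arm, n = 2(1.96 + 0.84)² SD² / 0.5²:

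| SD before factors (mmol/L) | Factors not in definitive model | R² 0.10, factors in | R² 0.20, factors in |
|---|---|---|---|
| 0.75 | 36 | 32 | 29 |
| 1.0 | 63 | 57 | 51 |

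**The case against.** The strongest reply is that this is a condensed article. For the glycaemic outcomes it names ANCOVA and a reference but no covariates, so it excludes none, and the full list may stand in an analysis plan that is not shown. That is right. A reader might infer that every model adjusts for baseline values alone, but the text does not say so for mean 24-h glucose or the other CGM measures. Nor can "adjustment will be made for the primary outcome only" be taken as a covariate set that shuts the factors out, because it may mean only that the primary outcome alone is adjusted.

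It can also be said that trial entry measurements might include demographics, since these are collected at study entry. That reading is possible but strained in a sentence about dietary and activity outcomes, and nothing in it points to the minimisation factors.

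The reply is also right that the loss of width depends on prognostic strength, which the document does not give. All women have BMI of at least 30 and are selected by a risk score that includes age, which may weaken both as predictors. On the other side, age's place in the prediction model is some evidence that it carries information.

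Finally, efficacy is secondary here and the error is conservative. This limits the importance of the point but does not remove it. A stated adjustment rule that leaves out the allocation factors can be improved cheaply.

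**Conclusion.** The point holds in a conditional form. Allocation uses four factors, no stated model names them, and the diet and activity models have a stated adjustment that does not mention them. If the factors predict outcome beyond baseline, intervals that omit them are too wide by about 3 to 4%, 10% and 18% at partial R² of 0.10, 0.20 and 0.30, and by under 1% at 0.05. These sizes rest on the assumed R² range, 60 evaluable women and the assumed minimisation settings. Treatment estimates are not biased and false positives are not inflated.

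A reader might go further and conclude that the SD carried to the definitive trial will be too large. The documents do not support that. The SD they describe is that of mean 24-h glucose, which is essentially unbiased under minimisation and right for an unadjusted definitive analysis. It is larger than needed only if the definitive analysis adjusts, and that analysis is not described. What remains open is whether the within-arm or the residual SD is meant.

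**What to change.** In the ANCOVA for mean 24-h glucose, the other continuous CGM measures, diet and physical activity, adjust for the outcome's own baseline value and the minimisation factors. Enter age and BMI as continuous terms, parity as binary, and ethnicity with sparse groups merged. State this in the plan before the data are analysed.

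For the definitive trial, report both the within-arm SD of mean 24-h glucose and the residual SD from this model, and base the sample size on whichever matches the definitive analysis.

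Only analysis wording changes. The price is about 6 to 7 of 56 residual degrees of freedom. If the factors turn out to have no prognostic value, intervals will be about 2% wider.
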